### Sample size calculation

The sample size in this study was calculated using multiple regression to detect a difference of 3 in the mean plasma FA receptor level between groups with 80% power (α error = 0.05), a ratio of 2:1 between groups, and a coefficient of determination R^2^ of 0.10. Overall, a sample size of 100 mother-infant dyads is required: 70 mothers over 18 years of age giving birth before 29 GA and 30 mothers with full-term pregnancies (39–41 GA + 6 days).

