## Methods

### Study design

Initially, the OMEGAROP-2 clinical trial (NCT04819893) was a single-center prospective cohort study. However, ROP is an uncommon pathology, with an incidence of approximately 20% in preterm newborns under 29 GA. Therefore, our protocol was amended to extend recruitment from 22 to 46 months at the Dijon University Hospital Maternity Department and to make the study a multicenter project with the collaboration of the ophthalmology and gynecology departments of Necker Hospital, Paris, France, to increase the number of participants.

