#### Newborn follow-up

ROP screening will be performed with a wide-field RETCAM II camera (Clarity Medical Systems; Pleasanton, CA, USA) using a lid speculum after application of a local anesthetic (oxybuprocaine hydrochloride 1.6 mg/0.4 mL; Thea Laboratories, Clermont-Ferrand, France) only in premature infants because ROP does not occur in full-term infants. Pupillary dilation will be performed before hand using one drop of 2.5% epinephrine (phenylephrine 5% diluted to 2.5%; Europhta Laboratories, Monaco) and one drop of tropicamide (2 mg/0.4 mL; Thea Laboratories, Clermont-Ferrand, France). A trained nurse will complete the procedure, and a trained pediatrics-specialized ophthalmologist will analyze all fundus photographs. The initiation of ROP screening should be based on the infant’s postmenstrual age because the onset of severe ROP correlates better with postmenstrual age than with postnatal age [2]. The screening will begin at 4th weeks of life but never before 31 weeks of postconceptional age (PCA) and will be repeated every other week until 41 weeks’ PCA if no ROP was detected, and every week and up to twice a week in the case of ROP. ROP staging will be determined according to the International Classification of ROP consensus statement [37] (Table 3).

**Table 3 Tab3:** The International Classification of Retinopathy of Prematurity [37]

**Stage**		**Localization**		**Severity**	
1	Demarcation line	I	Circle area centered on the optic nerve with a radius twice the distance from the optic nerve to the macula	Plus disease	Sufficient vascular dilatation and tortuosity in at least 2 quadrants of the eye
2	Ridge	II	It extends from the end of zone I to the nasal ora serrata	Pre-plus disease	Insufficient vascular dilatation and tortuosity less than in plus disease
3	Extraretinal fibrovascular proliferation	III	It corresponds to the growing remaining crescent area		
4a	Extrafoveal partial retinal detachment				
4b	Foveal partial retinal detachment				
5	Total retinal detachment				

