## Objectives and statistical analysis

### Outcomes

The primary outcome is to evaluate the relationship between the expression level of placental FA receptors and ROP occurrence.

Secondary outcomes of the study are: (1) assessment of the relationship between blood cord FA content and the expression level of placental FA receptors; (2) assessment of the relationship between maternal blood FA content and the expression level of placental FA receptors; (3) assessment of the relationship between placental FA receptor expression levels and the occurrence and severity of ROP.

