## Statistical methods

The data will be reviewed at the end of the study before statistical analysis. Statistical analysis will be performed using STATA v15.1 (StataCorp, College Station, TX, USA).

Quantitative data will be expressed as median and interquartile range [IQR]. The groups will be compared for quantitative variables using parametric or non-parametric tests according to normal/abnormal data distribution, and for qualitative variables using the chi-square test or Fisher’s exact test. Spearman correlations will be used to analyze the extent to which the placental FA receptor expression is associated with ROP occurrence. The extent to which the placental FA receptor expression is associated with the maternal blood FA level and the blood cord FA level will be analyzed through Spearman correlations. Linear regression analyses will be carried out to compare placental FA receptor expression levels as a function of GA. Statistical significance is to be set at *p* < 0.05, and the tests will be two-tailed.

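### The stated 80% power is not a property of the primary ROP comparison: it rests on an unmeasured plasma variable and a 2:1 ratio, while the protocol's own incidence implies about 14 versus at most 56 dyads

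*Protocol article*

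**What the plan says.** The Sample size calculation says that multiple regression was used to detect "a difference of 3 in the mean plasma FA receptor level between groups with 80% power", with a two-group ratio of 2:1 and a coefficient of determination of 0.10. The resulting 100 dyads are split into "70 mothers over 18 years of age giving birth before 29 GA and 30 mothers with full-term pregnancies". The section does not name the two groups in the ratio, and it gives no SD, no unit for the difference of 3 and no number of predictors.

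Other sections bear on this:

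- **Outcomes:** the primary outcome is "the relationship between the expression level of placental FA receptors and ROP occurrence".
- **Placental lipid transport/receptor protein analyses:** receptors are quantified in placental tissue by Western blot.
- **Lipidomic blood analyses:** blood is used for red-cell fatty acid composition. No receptor assay in plasma is described.
- **Study design:** ROP is described as uncommon, "with an incidence of approximately 20% in preterm newborns under 29 GA".
- **Newborn follow-up:** eye screening is done "only in premature infants because ROP does not occur in full-term infants".
- **Study population and schedule:** the ROP group is type 1 or 2 ROP, and the preterm comparison group has no ROP of any stage.
- **Statistical methods:** the association between placental expression and ROP is to be analysed by Spearman correlation, and "the tests will be two-tailed".

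**The concern.** A power statement should describe the comparison that answers the primary question. This one names a variable the study does not measure and a group ratio that the article's own incidence contradicts. ROP cases can come only from the preterm dyads, and one in five of 70 is far from a 2:1 split.

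A reader who takes 80% at face value would assume a one-in-five chance of missing the planned effect. If the true chance is between a third and a half, a null result would carry much less weight against the placental-transfer hypothesis than the stated power suggests. Recruitment was still under way according to Trial status, so the statement can be corrected before results are known.

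**Working it through.** **Inputs from the article.** Two-sided α = 0.05 and power 80% ("80% power (α error = 0.05" in the Sample size calculation; two-tailed tests in Statistical methods). Difference 3, ratio 2:1, R² = 0.10, N = 100 split 70/30 (Sample size calculation). ROP incidence about 20% (Study design). **Not given:** SD, unit, number of predictors, identity of the two groups.

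**Step 1: can the 100 be reproduced?** Not from the stated inputs alone.

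- *Difference of 3 at 2:1.* Normal approximation, smaller group n = (1.96 + 0.842)² × (SD/3)² × (1 + 1/2). With an assumed SD of 5: 7.85 × 2.778 × 1.5 = 32.7, so 33 + 66 = 99. This works only because SD = 5 was chosen to fit.
- *R² = 0.10 as an overall regression test.* f² = 0.10/0.90 = 0.111, noncentral F. N for 80% power is 73, 90, 103 or 113 with 1, 2, 3 or 4 predictors. Three predictors come close (79% power at N = 100), but the number is not stated.
- *The split.* 70/30 = 2.33, not 2.

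**Step 2: the primary contrast.** 0.20 × 70 = 14 ROP and 70 − 14 = 56 without, a ratio of 1:4. Fifty-six is a maximum: if the 20% refers to type 1 or 2 ROP, infants with milder ROP belong to neither group and reduce the 56.

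**Step 3: power for 14 versus 56 under each reading.** Two-sample noncentral t, two-sided 5%, noncentrality = d / √(1/n₁ + 1/n₂), where d is the difference in SD units. For 14 versus 56, √(1/14 + 1/56) = 0.299. The effect d is back-solved from what the article states. For the R² readings, d = √(0.111 / [p(1 − p)]), with p the share of the smaller group: p = 1/3 gives √(0.111/0.222) = 0.707, and p = 0.20 gives √(0.111/0.16) = 0.833.

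| Reading of the 80% or of R² | d (SD units) | Implied SD (3/d) | Power, 14 vs 56 | Power, 14 vs 86 |
|---|---|---|---|---|
| 80% with 100 dyads at 2:1 (67:33) | 0.602 | 4.99 | 51% | 54% |
| 80% with 100 dyads at 70:30 | 0.617 | 4.86 | 53% | 56% |
| R² = 0.10 is the group effect at 2:1 | 0.707 | 4.24 | 65% | 68% |
| 80% at 2:1 within 70 preterm dyads (47:23) | 0.723 | 4.15 | 66% | 70% |
| R² = 0.10 applied directly to a 20:80 split | 0.833 | 3.60 | 78% | 82% |

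The last column counts the 30 term dyads as no-ROP (56 + 30 = 86). The last row does not use the stated 2:1 ratio.

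**Step 4: detectable effect.** For 14 versus 56, 80% power requires d = 0.85 SD.

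**Step 5: sensitivity to the unstated SD.** With the difference fixed at 3, power for 14 versus 56 is 91% at SD 3, 70% at SD 4, 51% at SD 5 and 38% at SD 6. These SDs are assumptions; the article gives none.

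**The case against.** The strongest reply is that the groups are never named, so nobody can say which comparison was sized. A reader might infer from the 70/30 split that the 80% belongs to preterm versus term. The article does not say so, and 70:30 is not exactly 2:1. Another reading fits about as well: R² = 0.10 as a single group effect at 2:1 inside the preterm cohort, where 47 versus 23 has 78% power, with the 30 term dyads added as a reference group. The fault would then be an optimistic ROP share (one third instead of one fifth), not the wrong contrast. That stands, and it is why the power is given by reading. It does not rescue the 80%, because that reading still leaves 14 versus 56 at about 65–66%.

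A reader might also quote 51–65% as the power of the study. That is too firm. The two ends rest on different back-solved effects: at 0.707 SD, 100 dyads split 70:30 would have 89% power, not 80%. With an SD of 3 the contrast would even exceed 80%, although an SD that small would need only 36 dyads at 2:1 and so does not fit a requirement of 100.

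It might be inferred, too, that the term dyads serve only a secondary comparison by prematurity. Neither Outcomes nor Statistical methods says so, and neither states whether term dyads enter the primary correlation. Finally, a condensed article may leave the SD and the number of predictors to the full protocol. Their absence alone is therefore no fault. The named variable and the ratio are on the page, and they conflict with the rest of the article.

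**Conclusion.** The point holds in this form: the 80% is not a property of the comparison of placental receptor expression by ROP status. The section names a plasma receptor level that no described assay measures, and its 2:1 ratio conflicts with the roughly 1:4 split that the article's own 20% incidence yields in 70 preterm dyads.

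Under every reading that keeps the stated 2:1 or 70:30 split, power for 14 versus at most 56 is about 51–66%. Counting term dyads as no-ROP raises this only to about 54–70% and mixes ROP with prematurity. Applying R² = 0.10 directly to a 20:80 split gives about 78% in the preterm dyads (82% if term dyads are also counted), but it discards a stated input.

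These figures assume 20% incidence, a full 56 in the comparison group and a t-test. The planned primary analysis is a Spearman correlation, so they are a guide and not exact. The exact power cannot be determined from the article, because the SD and the groups are not given.

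**What to change.** Revise the Sample size calculation as follows:

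1. Replace the plasma variable with placental FA receptor expression, and give the unit and SD behind the difference of 3.
2. Name the two groups compared.
3. Replace the 2:1 ratio with the expected ROP split, about 14 versus at most 56 among 70 preterm dyads.
4. Restate the power for that split: 80% only for about 0.85 SD, and about 51–66% for the planned effect, depending on which reading the sponsor confirms. If the sponsor holds the SD, a single figure can replace the range.
5. Note that these are t-test figures while the planned analysis is Spearman, or recompute for the planned analysis.
6. State whether term dyads enter the primary analysis.

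This changes wording only and needs no additional patients. The cost is a less favourable stated power.

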### Assessment of variables

#### Maternal history collection

Maternal history that may cause changes in placental function will be recorded, for example, pregnancy-induced hypertension, pre-eclampsia, abruptio placentae, and autoimmune and thromboembolic diseases during the pregnancy (Table 2). The investigator will give this document to the patient following delivery.

**Table 2 Tab2:** Maternal characteristics

**Inclusion number**	
**Age**	
**Pre-pregnancy weight (kg)**	
**End of pregnancy weight (kg)**	
**Size (cm)**	
**Smoking (during pregnancy)**	
**Alcohol (during pregnancy)**	
**Taking medication**	
**Multiple pregnancies?**	
**Delivery route**	
**Primipara?**	
**Diabetes (before pregnancy), if yes, HbA1c (%)**	
**Dyslipidemia**	
**Arterial hypertension**	
**Digestive diseases (please specify)**	
**Thromboembolic diseases**	
**Dysimmune diseases**	
**Obstetrical history (please specify)**	
Events during this pregnancy	
**Recurrent vomiting (what trimester? how often?)**	
**Gestational diabetes (specify if insulin is required)**	
**Maternal–fetal infection (specify)**	
**Gestational hypertension**	
**Pre-eclampsia**	
**Eclampsia**	
**Premature delivery risks**	
**Placental characteristics**	Birth weight (g): Weight at pathology analysis (g): Hypotrophic? Immature? Hematoma? Placental ischemia? Infection? (chorioamnionitis or funiculitis?)

#### Newborn follow-up

ROP screening will be performed with a wide-field RETCAM II camera (Clarity Medical Systems; Pleasanton, CA, USA) using a lid speculum after application of a local anesthetic (oxybuprocaine hydrochloride 1.6 mg/0.4 mL; Thea Laboratories, Clermont-Ferrand, France) only in premature infants because ROP does not occur in full-term infants. Pupillary dilation will be performed before hand using one drop of 2.5% epinephrine (phenylephrine 5% diluted to 2.5%; Europhta Laboratories, Monaco) and one drop of tropicamide (2 mg/0.4 mL; Thea Laboratories, Clermont-Ferrand, France). A trained nurse will complete the procedure, and a trained pediatrics-specialized ophthalmologist will analyze all fundus photographs. The initiation of ROP screening should be based on the infant’s postmenstrual age because the onset of severe ROP correlates better with postmenstrual age than with postnatal age [2]. The screening will begin at 4th weeks of life but never before 31 weeks of postconceptional age (PCA) and will be repeated every other week until 41 weeks’ PCA if no ROP was detected, and every week and up to twice a week in the case of ROP. ROP staging will be determined according to the International Classification of ROP consensus statement [37] (Table 3).

**Table 3 Tab3:** The International Classification of Retinopathy of Prematurity [37]

**Stage**		**Localization**		**Severity**	
1	Demarcation line	I	Circle area centered on the optic nerve with a radius twice the distance from the optic nerve to the macula	Plus disease	Sufficient vascular dilatation and tortuosity in at least 2 quadrants of the eye
2	Ridge	II	It extends from the end of zone I to the nasal ora serrata	Pre-plus disease	Insufficient vascular dilatation and tortuosity less than in plus disease
3	Extraretinal fibrovascular proliferation	III	It corresponds to the growing remaining crescent area		
4a	Extrafoveal partial retinal detachment				
4b	Foveal partial retinal detachment				
5	Total retinal detachment				

If necessary, transpupillary laser treatment of the ischemic areas will be performed under general anesthesia. This treatment will be carried out at the Fondation Ophtalmologique Adolphe de Rothschild, Paris, France; the treatment involves " + " attacks in zone I, stage 3 in zone I, and stages 2 and 3 " + " in zone II [38]. Significant risk factors for developing ROP, namely, term and weight at birth, duration of mechanical ventilation, sepsis, use of erythropoietin, red blood cell transfusion, and cerebral hemorrhage will be documented during the first month of life (Table 4).

**Table 4 Tab4:** Newborn characteristics

**Inclusion number**	
Date of birth	
Term of birth (GA)	
Birth weight (g)	
Fetal growth restriction	< 10th percentile? < 5th percentile? Causes: Maternal? Fetal? Placental?
Weight to W1/W2/W3/W4 (g)	
Gender	Male / Female
Oxygen therapy:	Total duration (days): Duration of mechanical ventilation (days): Duration of CPAP (days): Duration of HFNC (days): Duration of simple nasal cannula (days): Maximum FiO_2_ (%):
Sepsis	Yes/No
Necrotizing enterocolitis	Stage I / II / III? Required surgical management? Yes/No
Neurologic conditions	Intracranial hemorrhage (specify the grade): Periventricular hemorrhage (specify the grade): Subependymal hemorrhage (specify the grade): Periventricular leukomalacia (specify the grade):
Anemia	Minimum hemoglobin level: Transfusion (specify the number of units and quantity): EPO use?
Ophthalmologic follow-up	Date of first fundus: Week of life at first fundus: Week of gestation at first fundus: Date of fundus at first sign of ROP: Week of life at first sign of ROP: Week of gestation at first sign of ROP: Stage of ROP at first sign of ROP: Localization of ROP at first sign of ROP: Stage plus or pre-plus: ROP type 1 or 2: Most severe eye: Date of fundus at maximal ROP: Week of life at maximal ROP: Week of gestation at maximal ROP: Number of fundus before first sign of ROP: Number of fundus before maximal ROP: Total number of fundus with RETCAM: Laser treatment (which eye?): Date of laser treatment: Intravitreal treatment (bevacizumab) (which eye?): Date of intravitreal treatment:
Date of discharge (specify if transferred to another hospital)	

### Biochemical assessments

#### Maternal samples

A 0.5-mL cord blood sample will be collected by venipuncture at the time of delivery in an EDTA tube by a midwife or a gynecologist. A 5-mL blood sample will also be taken from mothers within a maximum delay of 2 days following delivery. Red blood cells will be immediately separated from serum, and samples will be stored at − 80 °C until lipidomic analyses. Three placenta samples (1 cm wide by 1 cm long) will be cut from mothers after delivery and stored at − 80 °C. Following the recommendations of the Ethical considerations for clinical trials on medicinal products conducted with minors,” the volume of blood collected will be limited to 0.5 mL for the umbilical cord blood and 5 mL for the mother’s venous blood [39].

#### Lipidomic blood analyses

The red blood cell FA composition for maternal and cord blood samples will be determined according to previously described procedures [36, 40]: Total lipids are extracted from erythrocytes, according to Moilanen and Nikkari [41]. Phospholipids are purified from total lipid extracts using silica cartridges [42], and transmethylated using boron trifluoride in methanol [43]. The fatty acid methyl esters (FAMEs) and dimethyl acetals (DMAs) are extracted with hexane and analyzed on a Hewlett Packard Model 5890 gas chromatograph using a CPSIL-88 column (100 mm × 0.25 mm i.d., film thickness 0.20 mm; Varian, Les Ulis, France) equipped with a flame ionization detector. Hydrogen is used as the carrier gas (inlet pressure 210 kPa). The oven temperature is held at 60 °C for 5 min, increased to 165 °C at 15 °C/min, held for 1 min, and then increased to 225 °C at 2 °C/min and finally kept at 225 °C for 17 min. The injector and the detector are maintained at 250 °C. FAMEs are identified by comparison with commercial and synthetic standards. The data will be processed using the EZChrom Elite software (Agilent Technologies, Massy, France) and reported as a percentage of the total FAMEs and DMAs [36, 40].

#### Placental lipid transport/receptor protein analyses

Proteins will be identified by Western blotting (WB). Tissues are previously treated with a modified RIPA buffer and stored at -80 °C. The samples are denatured by adding Laemmli (Bio-Rad, Hercules, CA, USA) 10 × low glycerol concentration. Proteins are deposited in each well (20 μg for each of the experimental conditions) and then separated according to their molecular weight by migration on an SDS Stain-Free acrylamide gel (Mini-PROTEAN TGX, Stain-Free 4–15% Gels, Bio-Rad, Hercules, CA, USA) at 70 V for 15 min, and then at 140 V for approximately 1 h. Proteins are then transferred to a 0.2-μm nitrocellulose membrane (reference 1,620,112, Bio-Rad, Hercules, CA, USA) using the Trans-Blot Turbo Transfer System (Bio-Rad, Hercules, CA, USA) in semi-dry condition at 2.5 A and 25 V for 7 min. The non-specific sites are saturated by incubating the membrane for 1 h at room temperature in 1% PBS-Tween 5% skimmed milk The proteins of interest are then revealed by the successive incubation of a primary antibody and then a secondary antibody. The primary antibodies specific to the protein of interest are diluted 1/1000 in 1% PBS-Tween 5% skimmed milk buffer and incubated overnight at + 4 °C. The secondary antibody specific to the primary antibody (polyclonal goat anti-mouse / HRP, Dako, reference P0447), coupled to a peroxidase (HRP) is diluted 1/1000 in 1% PBS-Tween 5% skimmed milk and then incubated for 1 h at room temperature. Chemiluminescent protein detection (ECL) is performed using a ChemiDocTM XRS reader with the Western lightning® Plus-ECL Enhanced Chemiluminescence Substrate (NEL 104001EA, Perkin-Elmer). Quantification of proteins of interest will be performed using the ImageLab® v.4.0.1 software.

## Objectives and statistical analysis

### Outcomes

The primary outcome is to evaluate the relationship between the expression level of placental FA receptors and ROP occurrence.

Secondary outcomes of the study are: (1) assessment of the relationship between blood cord FA content and the expression level of placental FA receptors; (2) assessment of the relationship between maternal blood FA content and the expression level of placental FA receptors; (3) assessment of the relationship between placental FA receptor expression levels and the occurrence and severity of ROP.

## Statistical methods

The data will be reviewed at the end of the study before statistical analysis. Statistical analysis will be performed using STATA v15.1 (StataCorp, College Station, TX, USA).

Quantitative data will be expressed as median and interquartile range [IQR]. The groups will be compared for quantitative variables using parametric or non-parametric tests according to normal/abnormal data distribution, and for qualitative variables using the chi-square test or Fisher’s exact test. Spearman correlations will be used to analyze the extent to which the placental FA receptor expression is associated with ROP occurrence. The extent to which the placental FA receptor expression is associated with the maternal blood FA level and the blood cord FA level will be analyzed through Spearman correlations. Linear regression analyses will be carried out to compare placental FA receptor expression levels as a function of GA. Statistical significance is to be set at *p* < 0.05, and the tests will be two-tailed.

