**Fig. 1 Fig1:**
[figure not shown]
Flowchart of the OmegaROP-2 study

For mother-infant dyads born before 29 GA, screening will be performed in the Pathological Pregnancy Department. Screening will be carried out in the delivery room for patients delivering at full-term. First, the investigating physician provides the patient with information and answers questions about the research study’s purpose and requirements. They also specify the patient’s rights when participating in biomedical research and verify the eligibility criteria. Second, the investigator obtains the patient’s freely given, informed, and written consent. Finally, the investigator provides a copy of the informed consent form according to article L1122-1 of the Public Health Code. Patients who do not consent to the trial will be treated according to standard care. The “prematurity ROP group” will be defined as patients with infants developing ROP type 1 or 2 (visible on fundus examination after 4 weeks of life and at least 31 GA) and born before 29 GA. The “prematurity no-ROP group” will be defined as patients with infants without any stage of ROP and born before 29 GA. The “full-term no ROP group” will comprise patients with infants without ROP and born at full-term. Mother-infant dyads in life-threatening conditions will not be included (Table 1).

**Table 1 Tab1:** Inclusion and exclusion criteria

Inclusion criteria	Exclusion criteria
Mothers delivering a premature newborn of less than 29 weeks’ gestational age (GA) after obtaining their non-opposition	Mothers giving birth between 29 and 38 GA + 6 days
Mothers giving birth at full term between 39 and 41 GA + 6 days, after obtaining their non-opposition	Mothers with a vital prognosis
The mother must be of legal age	The mother is not affiliated with a social security system
The mother must not be under legal guardianship	For full-term mothers: Current or previous history of an obstetrical pathology of any origin (vascular such as gestational hypertension, pre-eclampsia; gestational diabetes; intrauterine growth retardation, maternal infection during pregnancy such as toxoplasmosis, cytomegalovirus, rubella, measles, chickenpox)

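### The only method named for the primary relationship is an unadjusted Spearman correlation, so gestational age can create or hide an association between placental receptor expression and ROP

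*Protocol article*

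**What the plan says.** All places are in the protocol article.

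- **Outcomes:** "The primary outcome is to evaluate the relationship between the expression level of placental FA receptors and ROP occurrence".
- **Statistical methods**, on that relationship: "Spearman correlations will be used to analyze the extent to which the placental FA receptor expression is associated with ROP occurrence". No covariate, stratum or analysis population follows. The general between-group tests in the same section are also unadjusted.
- **Statistical methods**, the only analytic use of GA: "Linear regression analyses will be carried out to compare placental FA receptor expression levels as a function of GA". ROP is not named as a term in this model.
- **Newborn follow-up**, on risk factors to be recorded: "Significant risk factors for developing ROP, namely, term and weight at birth, duration of mechanical ventilation, sepsis", followed by others. No use of them in the analysis is stated.
- **Newborn follow-up**, on who is screened for ROP: "only in premature infants because ROP does not occur in full-term infants".
- **Study population and schedule** defines three groups. The third reads: "The “full-term no ROP group” will comprise patients with infants without ROP and born at full-term".
- **Sample size calculation:** "The sample size in this study was calculated using multiple regression", with an R² of 0.10, giving 70 preterm and 30 full-term dyads.

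**The concern.** A common cause of exposure and outcome distorts an unadjusted association. The protocol itself supplies one half of this for GA, as a risk factor for ROP. It treats the other half as plausible, because it plans to examine expression as a function of GA. Nothing in the stated ROP analysis separates the two. The GA regression does not do so either: it describes how expression changes with GA and does not estimate the ROP association at a given GA.

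The study is meant to point to a mechanism and a preventive target. A positive correlation could merely restate that less mature placentas go with less mature retinas. If the GA trend runs against the ROP effect, a real difference could be missed.

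Two further points add to this. The text does not say whether full-term dyads enter the correlation. The sample size rests on multiple regression, while no multiple regression of the primary relationship appears among the stated methods.

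**Working it through.** **1. The plan's own figure.** The total of 100 cannot be reproduced from the stated inputs alone, because the article gives no SD for the difference of 3 and no number of predictors. An overall F test in a regression with R² = 0.10, 80% power and α = 0.05 needs 73, 90, 103 or 113 dyads for 1, 2, 3 or 4 predictors. A comparison of two means at 2:1 gives about 100 if the SD is about 5.0. So 100 is compatible with a model of about three predictors, but the methods section describes no such model for the primary relationship. The point below does not depend on this.

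**2. Inputs.** From the protocol: 70 preterm dyads; ROP incidence about 20% below 29 weeks (Study design), hence 0.20 × 70 = 14 with ROP and 56 without; two-sided α of 0.05. Assumed, because the documents give no value: GA uniform from 24 to 29 weeks; expression changing by b = 0.15 or 0.30 residual SD per week; ROP odds 1.5 or 2 times higher for each week earlier.

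**3. Size of the distortion, by formula.** With no ROP effect at a given GA, the expected difference in expression between ROP and no-ROP infants is

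bias = b × (mean GA without ROP − mean GA with ROP).

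Averaging the logistic model over 24 to 29 weeks at 20% incidence gives a GA difference of 0.80 weeks at a 1.5-fold gradient (26.66 − 25.86) and 1.25 weeks at a 2-fold gradient (26.75 − 25.50). At b = 0.30 and a 2-fold gradient:

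- bias = 0.30 × 1.25 = 0.37 SD;
- total SD of expression = √(1 + 0.30² × 25/12) = 1.09, so the standardised bias is 0.37/1.09 = 0.34;
- standard error = √(1/14 + 1/56) = 0.299, so z = 0.34/0.299 = 1.15;
- probability of p < 0.05 ≈ P(Z > 1.96 − 1.15) = 21%.

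**4. Simulation, preterm dyads only, no ROP effect at a given GA** (4,000 runs per row; Monte Carlo standard error about 0.4 to 0.6 percentage points):

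| b (SD/week) | ROP odds per week earlier | Formula | Spearman, p < 0.05 | Regression with GA, p < 0.05 |
|---|---|---|---|---|
| 0 | 2 | 5% | 5.4% | 5.6% |
| 0.15 | 1.5 | 6.8% | 7.6% | 5.6% |
| 0.15 | 2 | 9.4% | 9.4% | 5.4% |
| 0.30 | 1.5 | 11.4% | 11.1% | 5.1% |
| 0.30 | 2 | 21.0% | 20.4% | 4.6% |

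Formula and simulation agree: about 7% to 21% unadjusted, about 5% with GA in the model, and no inflation when b = 0.

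**5. Hiding a real effect, preterm dyads only.** Let ROP lower expression by 0.6 SD. With no GA effect, the Spearman test has about 48% power. If expression also falls 0.30 SD per week of advancing GA, with a 2-fold ROP gradient, its power drops to about 10%. The GA-adjusted regression keeps about 45%.

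**6. If full-term dyads were pooled as ROP-free (not stated in the protocol).** With no ROP effect and no GA trend among preterm dyads, a term-preterm shift in expression of 0, 0.5, 1.0 or 1.5 SD gives a false-positive rate of 4.8%, 8.8%, 18.1% or 29.5%. With a true −0.6 SD ROP effect and term expression 1 SD lower, power is about 10%, against 47% in preterm dyads alone.

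**The case against.** The article condenses a fuller protocol, and an analysis plan may exist. A model with ROP and GA together may be written there, and the multiple regression in the sample size section hints at it. This is fair as far as it goes: a missing covariate list would be no finding. But the article does state a method for the primary relationship, that method is unadjusted, and the one regression it describes omits ROP.

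A reader might infer that full-term dyads will be counted as ROP-free in the correlation. The documents do not say so. They define three separate groups and say that the groups will be compared, which may point the other way. The pooled figures are therefore conditional, and what stands is that the analysis population is unstated.

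A reader might also infer that a Spearman coefficient against a yes/no variable is an invalid test. It is not. It works essentially as a rank-sum comparison. Its ceiling (0.69 for 14 of 70, 0.60 for 14 of 100) affects how the coefficient is read, not its p-value.

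Every bias figure rests on gradients that the protocol does not give, and enrolment below 29 weeks already narrows GA. Both are true. False-positive here means rejection when there is no ROP association at a given GA; the crude association is then real but due to GA. The protocol does not label the correlation as primary; that follows from matching it to the primary outcome. The 14 versus 56 split is also approximate: the ROP group requires type 1 or 2 and the no-ROP group requires no stage at all, so milder ROP falls in neither.

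**Conclusion.** The concern holds in this form: the method stated for the primary relationship ignores a risk factor that the protocol itself names and that may also drive expression. Among preterm dyads, under the assumed gradients, the false-positive rate is about 7% to 21% instead of 5%. In an adverse but plausible case, power for a 0.6 SD effect falls from about 48% to about 10%. If expression does not vary with GA below 29 weeks, there is no inflation; the documents do not settle which case applies. Pooling full-term dyads would add bias, but it is an open question in the text, not a stated step. It would go too far to say that the primary question cannot be answered: GA is recorded for every infant, so the remedy needs only wording.

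**What to change.** State as the primary analysis, in preterm dyads only, a linear regression of placental receptor expression (log-transformed if skewed) on ROP status, adjusted for GA at birth as a continuous variable and for centre. Report the adjusted difference with its 95% CI.

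Keep the Spearman correlation as descriptive, and the full-term group as a descriptive reference outside this model. Use growth restriction and pre-eclampsia only in a sensitivity analysis, with the reason stated: the newborn form lists the placenta among the causes of growth restriction, and both may lie on the pathway under study, so adjusting for them could remove part of the effect sought. Align the sample size section with this model. If the full protocol or analysis plan already specifies it, say so there and confirm the population.

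Cost: one or two degrees of freedom out of about 70 and a modest loss of precision (in the simulation with no GA trend, power was about 49% to 50% adjusted and 47% to 49% for Spearman; with a confounding trend, about 45% adjusted). No new data are needed. Precision remains limited by about 14 ROP cases, so few further covariates can be carried. Inclusion is still open and analysis waits for the data review at the end of the study, so the change can be fixed before the data are seen.
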